### Ethics and Dissemination

#### Ethics Approval and Consent to Participate

All procedures were approved by the ethics committees of the 5 clinical sites in the 3 countries involved (Italy, Netherlands, and Spain):

Maastricht UMC+ (the Netherlands)—Cardiothoracic Surgery DepartmentHospital Universitario Reina Sofia (SAS; Spain)—Cardiothoracic Surgery DepartmentINRCA (Italy)—Urology DepartmentSant Joan de Déu Hospital (Spain)—Orthopedics and Traumatology Department for ChildrenFundació Parc Taulí (Parc Taulí; Spain)—Orthopedics and Traumatology Department for Adults.

Spanish regulation allows only 1 ethics committee to be requested per country, and its approval applies to the national territory. Approval in Spain was requested by the Hospital Reina Sofía (SAS) ethical committee (Stars-car-0320-5113) and has been acknowledged by both Hospital Sant Joan de Déu and Parc Taulí ethical committees.

Signed consent was obtained from all participants in the study. For those who are unable to provide informed consent, the caregiver will approach each potential participant and his or her substitute decision maker to provide information on the study. If these potential participants and their substitute decision makers provide their consent, the substitute decision makers will sign the consent form, and the HCPs will seek the potential participants’ assent. Participants will not receive any incentive to participate in this study.

#### Withdrawal From the Study

The participants and substitute decision makers can request to withdraw from the study at any time, either orally or in writing. The participants will be able to withdraw from the study at any time before the group analysis is calculated. If a participant withdraws, his or her information will not be considered in the analysis. If a participant requests to have his or her data be destroyed, the research team will honor this request by shredding and recycling the paper records and erasing any records stored on a computer hard drive using commercial software applications designed to remove all data from storage devices. However, once all the participants’ data were analyzed, the participant could not withdraw. Participants will be informed of this condition in a consent letter. The deadline date for withdrawal will be determined once all participants’ data have been collected, and data analysis is underway. This will occur during the 6 months of the study.

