#### Experimental (Intervention) Group

The experimental group will receive a digital health solution during the first visit, and training on how to use this tool will be provided. Patients will take the digital health solution home with them and can use it as often as they like. The experimental group, after each 1 of the 4 standard care visits, will complete the same questionnaires as the control group.

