### Data Analyses

The analyses will be conducted in Python 3.9.5 through the IDE PyCharm Community Edition 2021.2.1 Software and intention-to-treat principles. Descriptive statistics will be used to characterize the groups during the 4 visits. Furthermore, owing to the small sample size, Spearman correlations will be performed with all the variables to check, first, for potential associations between the variables and, second, differences between the intervention versus control groups. Further potential differences between these groups will be analyzed as follows:

Stress (VAS), pain (VAS), and mood state (PANAS-short form) will be subjected to a multivariate mixed analysis of variance (split-plot ANOVA) with “time” as a within-subject factor (ie, 4 time points) and “group” as a between-subject factor (intervention vs control).Patient activation (PAM-13) and self-efficacy (GSE-SF) will also be submitted to a multivariate mixed analysis of variance with “time” as a within-subject factor (Ie, 3 time points) and “group” as a between-subject factor (intervention vs control).Mental well-being (Short Warwick Edinburgh Mental Well-Being Scale) and HRQoL (EQ-5D-3L and EQ-5D-Y) will be analyzed using multivariate mixed analyses of covariance. As measurements of these 2 variables are based on a pre-post design, postmeasurements will be used as the dependent variable and premeasurements as covariates.

Finally, it is of interest to explore the effects as a function of different types of surgery. To this end, 2 different statistical approaches will be used:

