Cluster analyses per surgery type. Data will be split for each of the surgeries, and variables will be analyzed individually using time and group as within and between factors, respectively.A different statistical approach from the approach described above will also be used. In this case, analyses are performed within a linear mixed model (LMM) framework. LMM allows for the flexible handling of unbalanced data, outliers, or missing observations without averaging the data of participants. In addition, LMM enables the modeling of data using different fixed and random factors. Accordingly, each of the variables will be submitted to an LMM analysis wherein “time,” “group (intervention vs control)” and their interaction (time × group) will be included as fixed factors. In contrast, “subjects” and “surgery” will be submitted as random factors. This analysis enables the calculation of regression estimation parameters by considering that participants differ in the surgery type. In addition, the participants’ age or sex may also be used as control covariates.

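### The withdrawal rule removes all data of anyone who withdraws, which cannot be reconciled with the stated intention-to-treat analysis and may bias the comparison in either direction

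*Protocol article*

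**What the plan says.** The analysis principle stands in the first sentence of Data Analyses: "The analyses will be conducted in Python 3.9.5 through the IDE PyCharm Community Edition 2021.2.1 Software and intention-to-treat principles".

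Withdrawal From the Study then sets four rules:

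- Exclusion: "If a participant withdraws, his or her information will not be considered in the analysis".
- Destruction, as a further and separate step: "If a participant requests to have his or her data be destroyed, the research team will honor this request".
- Window: "The participants will be able to withdraw from the study at any time before the group analysis is calculated".
- Cut-off: "The deadline date for withdrawal will be determined once all participants’ data have been collected, and data analysis is underway".

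On incomplete data, Data Analyses says of the linear mixed model (LMM): "LMM allows for the flexible handling of unbalanced data, outliers, or missing observations without averaging the data of participants". That model is introduced for exploring effects by type of surgery. The main group comparisons are split-plot ANOVAs and analyses of covariance.

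The arms differ in what participants receive: "The experimental group will receive a digital health solution during the first visit, and training on how to use this tool will be provided". Controls do not use the digital solution. Visits and questionnaires are the same in both arms.

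**The concern.** Intention-to-treat keeps every randomised participant in the arm assigned. The withdrawal rule takes some of them out after randomisation, together with outcomes already collected. Nothing in the article limits the exclusion to data after withdrawal, or says which rule has priority. A statistical analysis plan that follows one section would breach the other.

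The exclusion is also wider than data protection requires. A participant who stops but is content for earlier answers to be used is removed just like one who asks for destruction.

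Two things are at stake. Collected outcomes are lost from a trial with only 30 participants per arm. And the comparison of stress, pain and anxiety may be distorted if those who withdraw differ from those who stay, and do so differently by arm. Because the cut-off date is set only when analysis is under way, the analysis set is not fixed when the analysis starts.

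**Working it through.** **1. The two rules side by side.** Take a participant who completes baseline, admission and discharge, then asks to leave and does not ask for destruction. Under intention-to-treat, the three completed visits are analysed in the assigned arm. Under the withdrawal rule, none is. A participant who completes all four visits and withdraws before the group analysis loses a full record. The LMM does not resolve this: it can use a partial record, but not one that has been removed.

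**2. When the exclusion biases the comparison.** Let w be the fraction withdrawn in an arm, W the mean of those withdrawn and R the mean of those retained. The full-arm mean is (1 − w)R + wW, so

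retained mean − full-arm mean = −w × (W − R).

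The shift is zero if W = R. The group difference is unbiased if the shift is the same in both arms. The sign follows the sign of W − R and the arm in which withdrawal is heavier.

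Example: 5 of 30 withdraw, with stress 20 mm above those retained. The shift is (5/30) × 20 = 3.3 mm. If the 20 mm is measured against the full-arm mean instead, it is (5/25) × 20 = 4.0 mm.

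**3. Illustrated size.** The article states no withdrawal rate and no SD, so there is no figure of its own to reproduce. Assumptions: normally distributed stress VAS, SD 25 mm, no true effect, withdrawal in one arm only, and log-odds of withdrawal rising by 0.5 or 1.0 per SD of stress, with the intercept set to give the overall rate. Change in the retained mean, by numerical integration:

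| Withdrawn | Slope 0.5 | Slope 1.0 |
|---|---|---|
| 10% | −1.2 mm | −2.3 mm |
| 15% | −1.8 mm | −3.3 mm |
| 20% | −2.4 mm | −4.3 mm |

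At 15% to 20% the range in SD units is 1.8/25 = 0.07 to 4.3/25 = 0.17. With the slope reversed (less stressed people leave), each entry changes sign and keeps its size. The standard error of the group difference is 25 × √(2/30) = 6.5 mm, so the largest entry is 4.3/6.5 = 0.66 of one standard error.

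**4. Effect on the test.** This comes from a simulation of 40,000 trials with 30 per arm, no true effect and a two-sided t-test at 0.05. The stated share of an arm with the highest withdrawal tendency is deleted; that tendency has correlation rho with the outcome.

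| Deleted, intervention / control | rho | Bias (SD) | Type I error |
|---|---|---|---|
| 0% / 0% | 0.5 | 0.00 | 0.048 |
| 10% / 0% | 0.5 | −0.09 | 0.069 |
| 20% / 0% | 0.5 | −0.17 | 0.097 |
| 20% / 10% | 0.5 | −0.08 | 0.068 |
| 20% / 20% | 0.5 | 0.00 | 0.056 |
| 20% / 0% | 0 | 0.00 | 0.051 |
| 20% / 0% | 1 | −0.34 | 0.280 |

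The last row removes exactly the most stressed participants and is an extreme.

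**5. What these figures compare.** Steps 3 and 4 set deletion against complete outcomes on everyone. Keeping data up to withdrawal does not give complete outcomes. Someone who leaves between baseline and admission contributes no outcome after baseline under either rule. Someone who withdraws after the last visit contributes everything under the fix and nothing under the present rule. How much of the shift the rule itself causes depends on when people withdraw, which the article cannot tell us.

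**The case against.** The case for leaving the text alone has several parts, and most of them limit the point without removing it.

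- **Scope.** The rule applies to people who ask to withdraw. It does not apply to those who stop using the app, miss a visit or are lost to follow-up. Use of the tool is voluntary, so disliking it does not require leaving the study, and 15% to 20% may be too high for formal withdrawal. This stands as a limit on size.
- **Direction.** A reader might infer that the exclusion favours the programme, since the burden of app, headset and watch falls on one arm. The article does not support that. Less stressed patients may see no need for the tool and leave, or stressed controls who receive nothing extra may leave; either would push the other way. Only the possibility of bias is shown.
- **Size.** A reader might take the 2 to 4 mm as the effect of the rule. It is not, for the reason in step 5. It is also below one standard error of the comparison.
- **Retention.** A reader might infer that the rule hides retention, which matters in a feasibility trial. It does not follow: withdrawn participants leave the analysis, but they can still be counted by arm, and Quality Assurance and Safety commits to CONSORT reporting for feasibility trials.
- **Consent.** Removal may have been promised in the signed consent, whose wording is not shown. If so, that promise binds, and the intention-to-treat statement is what has to change.

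None of this reconciles the two sections.

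**Conclusion.** The contradiction is real and does not rest on any assumption: the article promises intention-to-treat and also prescribes removal of every participant who withdraws, whether or not destruction is requested. Bias is a possibility, in either direction. It requires withdrawal that is related to outcome and differs by arm. That is plausible because participants know their arm, report their own outcomes, and only one arm receives the tool.

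The size is illustrative: roughly 2 to 4 mm, or 0.07 to 0.17 SD, at an assumed 15% to 20% withdrawal in one arm and an assumed SD of 25 mm. This is an upper illustration, because it is measured against complete data. In a feasibility study with a modest illustrated shift, this is a should-fix. It needs settling now, since the article reports recruitment as complete and analysis as ongoing.

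**What to change.** Replace the exclusion sentence in Withdrawal From the Study with: *Data collected up to withdrawal are kept and analysed in the arm assigned, unless the participant withdraws permission to use them or asks for destruction; such cases are counted and reported by arm.*

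Then:

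- Include the partial records through the LMM already described, at least as a supporting analysis of all randomised participants, and state the missing-data assumption for visits after withdrawal. The LMM now serves the exploration by surgery type, so this extends its role; it is not already the main analysis.
- Fix the withdrawal cut-off date before analysis starts.
- If the signed consent promised removal, keep that promise. Drop the intention-to-treat label, report withdrawals and reasons by arm, and add a sensitivity analysis over a range of outcomes for the excluded participants.

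Cost: a short text change, a little more analysis work and possibly an ethics notification. No new data are needed.

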#### Consent or Assent

Signed consent will be obtained from all participants in the study. For those who are unable to provide informed consent, the caregiver will approach each potential participant and his or her substitute decision maker to provide information on the study. If these potential participants and their substitute decision makers provide their consent, the substitute decision makers will sign the consent form, and the HCPs will seek the potential participants’ assent.

#### Confidentiality

Participants will be assigned an alphanumeric code instead of using their names or other identifiers. Only the study coordinator will have access to the master list, where these codes are linked to the participants’ first names. With the exception of direct conversations with each participant, their names will not be used, only their numbers. Hard copies of the consent forms, questionnaires, and study notes will be stored in a locked filing cabinet in the 5 departments of the 5 hospitals. All of the deidentified electronic study documents will be encrypted and stored on a password-protected computer drive.

#### Access to Data

Participating HCPs will be given access to cleaned data sets. The master list will be stored on a password-protected computer. Only the study coordinator will have access to the master list. The data will be retained for 5 years and will be published in peer-reviewed journals and conferences. The data will not become part of a data repository and will not be involved in the creation of a research database or registry for future research. After 5 years, the data will be destroyed.

#### Quality Assurance and Safety

We will follow the CONSORT (Consolidated Standards of Reporting Trials) guidelines for clinical trial feasibility.

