#### Exclusion Criteria

Potential participants who are unable to provide informed consent; communicate in the native language; demonstrate basic digital literacy; present symptoms of dementia; are allergic to dedicated wearable materials, such as steel and silicone; are pregnant; and are enrolled in another clinical trial will be excluded.

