### Outcome Variables

#### Research Question 1 (Primary and Secondary Outcome Variables)

Stress, anxiety, and pain represent the primary outcome variables that will be measured using paper-and-pencil questionnaires.

The secondary outcome variables were overall quality of life, emotional status, mental well-being, self-efficacy perception, and patient activation during and after hospital stay.

To assess the primary outcome variables, the following questionnaires will be used after each standard care visit and will be administered by paper and pencil:

Patients’ and caregivers’ *self-reported stress* was measured using a VAS at enrollment (baseline), at admission for surgery, at hospital discharge, and 2 weeks after surgery. Operationally, a VAS is usually a horizontal line, 100 mm in length, anchored by word descriptors at each end, such as no stress versus highest stress possible [37].Patients’ *self-reported pain* was measured using a VAS for pain measurement at enrollment (baseline), at admission for surgery, at hospital discharge, and 2 weeks after the surgery. The VAS for pain is a validated single-item scale that is anchored by “no pain” (score of 0) and “pain as bad as it could be” or “worst imaginable pain” (score of 100). The VAS presents a high internal consistency, as shown by a Cronbach α of 0.9117 [38].Patients’*Hospital Anxiety and Depression Scale* (HADS) scores were measured at admission for surgery, at hospital discharge, and 2 weeks after surgery. The HADS consists of 2 dimensions with 7 questions each, one representing the anxiety subscale and the other representing depression, with both psychopathological concepts of anxiety and depression being independent. Each item was rated on a 4-point frequency scale, ranging from 0 to 3. The internal consistency of the HADS, as measured by the Cronbach α coefficient, was found to be .78 for the anxiety subscale and .86 for the depression subscale, indicating satisfactory reliability [39].

To assess the secondary outcome variables, the following questionnaires will be used after each standard care visit and will be administered paper and pencil:

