#### Research Question 2 (Usability Outcome Variables)

The usability of the intervention tools will be monitored during hospital stay and posthospitalization using well-validated and ad hoc metrics. The *System Usability Scale*, *Net Promoter Score*, and an ad hoc *usability questionnaire* will be administered to the intervention group patients and caregivers as well as the HCPs who are involved in the care management of the intervention group [45,46].

The System Usability Scale is a 10-item evaluation based on a 5-point Likert scale measuring the strength and agreement of usability [45].

The ad hoc *usability questionnaire* assessed 4 dimensions: (1) functionalities, (2) design, (3) manual and instruction for use, and (4) general usability on a Likert scale (1-10). Each dimension also contained open fields to which participants responded qualitatively.

Net Promoter Score is used to assess general satisfaction with the question, “How likely are you to recommend this service?” [46]. The response format ranged from –100 to +100. Specific satisfaction was measured using a Likert scale (0-100) on a single question (“Did the user like the CARINAE solution?”).

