#### Confounding Variables

Patient age, sex, surgery type, medication use, length of hospital stay, and health outcomes, such as postoperative complications, reoperation, mortality, and groups in which the patients were involved during the intervention, will be used as confounding variables.

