### Conclusions

This protocol defines the application of a very innovative approach to the management of stress associated with painful and stressful medical procedures, such as surgery. The project depicted in this manuscript proposes an excellent tool that companies and the health care system can use to collaborate on promoting the entry of this valuable technology into the global health care system market.

In conclusion, this study will provide valuable information on the effects of digital health interventions in comparison with the standard of care. A great deal of insights on the comparative effects of the tool on relevant outcomes and the usability of the comprehensive digital health solution by patients, caregivers, and HCPs will be acquired. This will contribute to the evidence planning process, which is crucial for future adoption of digital health programs.

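### Complications, reoperations and deaths after randomisation are treated as confounders, and no harm or tolerability outcome is named for a feasibility trial of VR and wearables

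*Protocol article*

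**What the plan says.** All references are to the protocol article.

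- **Quality Assurance and Safety** consists of one sentence: "We will follow the CONSORT (Consolidated Standards of Reporting Trials) guidelines for clinical trial feasibility".
- **Primary outcomes:** "Stress, anxiety, and pain represent the primary outcome variables that will be measured using paper-and-pencil questionnaires".
- **Secondary outcomes:** "The secondary outcome variables were overall quality of life, emotional status, mental well-being, self-efficacy perception, and patient activation during and after hospital stay".
- **Usability outcomes** are the System Usability Scale, the Net Promoter Score and an ad hoc questionnaire covering "1) functionalities, (2) design, (3) manual and instruction for use, and (4) general usability on a Likert scale (1-10". Of that questionnaire the article adds: "Each dimension also contained open fields to which participants responded qualitatively".
- **Confounding Variables** puts "health outcomes, such as postoperative complications, reoperation, mortality" in the same list as age, sex and surgery type.
- **Table 1** has four blocks: primary, secondary, usability and covariates. Clinical data reported by health care professionals at all four visits sit in the covariate block.
- **Exclusion Criteria** rule out people who "are allergic to dedicated wearable materials, such as steel and silicone".
- **Discussion, Overview** gives the primary objective as the feasibility of the programme and its wearable, mobile and VR technologies. **Conclusions** says of the findings: "This will contribute to the evidence planning process, which is crucial for future adoption of digital health programs".

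**The concern.** There are two linked problems.

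The first is the role given to complications, reoperation and death. A confounder is related to both treatment and outcome without being a consequence of treatment. Randomisation comes at the start and these events come after it, so they cannot have influenced allocation, and the intervention might influence them. Adjusting for them can remove part of a real effect on stress, anxiety or pain, or can introduce bias through other causes that the event and the outcome share. It also takes them out of the place where a reader looks for harms.

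The second is that nothing in the outcome list is a harm or a tolerability measure. Patients take the system home with no limit on use, before and after surgery, from age 8. The allergy exclusion shows that the authors recognised a risk from the wearable. A feasibility result that will inform later planning should be able to say how many patients had discomfort from the headset or a skin reaction to the watch, and how many stopped using a device because of it.

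**Working it through.** **Step 1: look for a harm or tolerability outcome.**

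| Place | Content | Harm or tolerability outcome named? |
|---|---|---|
| Table 1, primary; Research Question 1 | Stress, pain, anxiety and depression | No |
| Table 1, secondary; Research Question 1 | Quality of life, affect, well-being, self-efficacy, activation | No |
| Table 1, usability; Research Question 2 | Usability, recommendation, satisfaction | No; open fields only |
| Table 1, covariates | Demographics, clinical data, length of stay | Clinical data, as covariates |
| Confounding Variables | Complications, reoperation, mortality | Listed as confounders |
| Data Analyses | Mixed ANOVA and ANCOVA, linear mixed model, generic descriptives and Spearman correlations | No |
| Quality Assurance and Safety | Reporting guideline | No |

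That complications reach the database through the professionals' clinical report is an inference from Table 1 and Confounding Variables taken together. The article does not say so outright.

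**Step 2: check the confounder role against timing.** The order is consent, randomisation, surgery, then complication, reoperation or death. All three events therefore follow allocation. Mortality fails as a covariate for a further reason: every patient who completes the questionnaire two weeks after surgery is alive, so death by that visit does not vary among those with a score. Data Analyses names only age or sex as possible control covariates in the linear mixed model. The article thus calls these events confounders without showing the model they would enter.

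**Step 3: check the other routes by which events could surface.**

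- Open fields in the usability questionnaire: intervention-arm patients, their caregivers and staff; unprompted on harm as far as the article shows.
- App self-reports of complications and wound healing, and the chat: intervention arm only, because controls do not use the digital solution. No analysis is attached.
- Descriptive statistics by group, and Spearman correlations across all variables: these could include the clinical data in both arms, but they do not make any event a safety outcome.

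**Step 4: what 30 exposed patients could show.** The input is 30 intervention patients (Methods, Overview). The event rates r are assumptions, since the article gives none.

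Chance of seeing at least one event: 1 − (1 − r)^30.

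- r = 1%: 1 − 0.99^30 = 26%
- r = 5%: 1 − 0.95^30 = 79%
- r = 10%: 1 − 0.90^30 = 96%
- r = 20%: 1 − 0.80^30 = more than 99%

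Exact upper 95% limit with 0 of 30 events:

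- one-sided: 1 − 0.05^(1/30) = 9.5%
- two-sided: 1 − 0.025^(1/30) = 11.6%

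With 3 of 30 events, the exact (Clopper-Pearson) 95% interval is 2.1% to 26.5%.

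The article has no safety figure of its own to reproduce.

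**The case against.** The strongest reply is that this is a condensed article. Adverse-event definitions, forms and reporting procedures usually sit in the full protocol, and the summarised SPIRIT table is an appendix that is not shown. This stands as far as procedures go: their absence here is no finding. It does not answer what the article states, namely a confounder role for events after randomisation and an outcome list without a harm.

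A reader might infer more than the text supports:

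- *That the trial can say nothing about tolerability.* The items of the ad hoc questionnaire are not reproduced, so a comfort question cannot be ruled out, and the open fields may catch complaints.
- *That complications will never be compared between arms.* The group descriptives and the correlations across all variables may include them, if crudely.
- *That the professionals' reports are the only harm data.* App self-reports, wound pictures and the chat also exist, in the intervention arm.
- *That the one sentence on CONSORT is all the safety provision there is.* It is all that this section of the article contains; the full protocol may hold more.
- *That an adoption decision will follow directly.* The article claims only a contribution to evidence planning.

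Two practical objections also stand. Recruitment is complete and the last visit is 14 days after surgery, so a new question may come too late. And prompting for symptoms in one arm, then comparing counts by arm, would create a difference through ascertainment alone.

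**Conclusion.** The point holds in a limited form. The article gives events after randomisation a role they cannot have in a randomised comparison. It names no harm or tolerability outcome, although feasibility of VR and wearables is its stated objective. The other routes by which events may surface are unsystematic, and those through the app and the usability forms do not cover controls.

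The size is best put as information forgone: with a direct item and no events in 30 patients, a tolerability problem could be bounded at 9.5% (one-sided) or 11.6% (two-sided), whereas the outcomes as named support no bound. This assumes that all 30 patients are exposed and answer. The limits widen if some do not, and the withdrawal rule, which leaves the information of those who withdraw out of the analysis, makes that more likely. No bias in the stress, anxiety or pain results can be quantified, because the article gives neither event rates nor the model in which these variables would be used.

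**What to change.** 1. **Confounding Variables and Data Analyses:** remove complications, reoperation and mortality from the adjustment set. Report the events recorded by health care professionals by arm, as descriptive safety outcomes, with counts and exact confidence intervals and no hypothesis test. This needs no new data if the clinical report holds these events, and it can be done with analysis already under way.
2. **Device tolerability:** report headset discomfort, skin reaction to the watch, and use stopped because of either, in the intervention arm only, as single-arm proportions with exact intervals. Use a short item on existing forms if data collection allows.
3. **If collection has closed:** draw on the open fields and on recorded withdrawal reasons, as far as these are retained and may be used. State in Limitations that tolerability was not asked systematically. Carry the item into the future definitive trial.
4. **Any general adverse-event question** must be asked identically in both arms.
5. **Quality Assurance and Safety:** keep CONSORT as the reporting standard, and refer to the outcomes above for what is measured.

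The cost is one extra table and, where an item can still be added, a slightly longer questionnaire.
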